## I. Outcome evaluation plan – prepared by the VUB

Section I contains the outcome evaluation plan. This section includes the statistical analysis plan to evaluate the outcome of 'PACE Steps to Success' palliative care programme as described in WP3 of the Annex I of the Grant Agreement and to assess whether or not outcomes vary between different sub-groups. Figure 1 illustrates the data collection methodology used for the outcome evaluation.

[figure not shown]

Figure 1. Data collection methodology for the outcome evaluation of PACE

## STATISTICAL ANALYSIS PLAN

### Hypotheses for primary outcome measures

**Hypothesis 1:** Quality of dying of residents as evaluated by staff is better in facilities using the 'PACE Steps to Success' palliative care programme than facilities which provide care as usual compared to baseline.

**Hypothesis 2:** Staff attitudes and knowledge towards palliative care are better in facilities using the 'PACE Steps to Success' palliative care programme than facilities which provide care as usual compared to baseline.

### Hypotheses for secondary outcome measures

**Hypothesis 3:** Quality of end-of-life care as evaluated by relatives is better in facilities using the 'PACE Steps to Success' palliative care programme than facilities which provide care as usual compared to baseline.

### Primary outcome measures

**Hypothesis 1:** Quality of dying of residents

The outcome measures to test hypotheses 1 include several aspects of quality of dying of the residents of the participating long-term care facilities (LTCFs).

- End-of-Life in Dementia – Comfort Assessment in Dying (EOLD – CAD)
  - Comfort during the last 7 days of life
  - Answered by the staff most involved in care and the most closely involved relative of the deceased resident at baseline, month 13 (T1), and 17 (T2)
- Quality of Dying in Long-Term Care (QOD – LTC):
  - Quality of dying in long-term care
  - Answered by the staff most involved in care for the deceased resident at baseline, month 13 (T1) and 17 (T2)

**Hypothesis 2:** Staff attitudes and knowledge towards palliative care

The outcome measures to test hypotheses 2 include several aspects of the attitudes and knowledge towards palliative care of staff in the participating LTCFs. These outcome measures were answered by all care staff present in participating LTCFs during data collection at baseline and month 12.

- End-of-Life Professional Caregiver Survey (ECPS)
  - Staff attitudes towards patient and family communication, cultural, and ethical values
- Palliative Care Survey (PCS)
  - Staff knowledge on palliative care
- Self-Efficacy in End-of-Life Care Survey (S-EOLC)
  - Staff confidence in communicating with residents and families about end-of-life (i.e. self-efficacy)

**Secondary outcome measures**

**Hypotheses 3:** Quality of end-of-life care

The outcome measure to test hypotheses 3 includes an aspect of the quality of end-of-life care.

- End-of-Life in Dementia – Satisfaction with Care (EOLD – SWC)
  - Evaluation of the quality of end-of-life care
  - Answered by the most closely involved relative of the deceased resident at baseline, month 13 (T1) and 17 (T2).

**Sample**

**Hypothesis 1:** To test hypotheses 1, all deceased residents for whom the staff most involved in care for the deceased resident completed a questionnaire will be included in the sample.

**Hypothesis 2:** To test hypotheses 2, all care staff present in participating LTCFs during data collection, who completed a questionnaire regarding their attitudes and knowledge towards palliative care, will be included in the sample.

**Hypothesis 3:** To test hypotheses 3, all deceased residents for whom the most closely involved relative of the deceased resident completed a questionnaire will be included in the sample.

## **Data analyses**

### **Step 1.** Exploring the data and data assumptions

The nature of each variable, as well as the influence of certain data assumptions on the study results must be explored prior to primary data analyses.

**Step 1.1.** Explore the number of cases in T1 and T2 to determine statistical power for each post intervention measurements. T1 and T2 can be used separately for the analysis when statistical power is at least 80%.

**Step 1.2.** Due to potential turn-over of staffs in LTCFs, the samples – care staffs present in participating LTCFs during data collection– with both the baseline and post-intervention measurements will be explored.

**Step 1.3.** Check data assumptions for regression analyses.

**Normality of distribution** – For continuous variables, a graphical representation (histogram) or the Shapiro Wilk-test or Kolmogorov Smirnov test can be used to check for normality of the distribution. If the normality of distribution is violated, log-transformation may for example be done. The partner responsible for conducting the analysis would need to discuss in the consortium on how skewed data can further be used for the analysis.

**Linearity** – Linearity between the outcome measures and the intervention variable or covariates will be checked through visual inspection of the scatter diagram. If the assumption of linearity is violated, the partner responsible for conducting the analysis would need to discuss in the consortium on how these data can be further used for the analysis – e.g. transforming into quartiles.

**Step 1.4.** Prepare the variables to be used for the data analyses based on the exploration of data and data assumptions.

### **Step 2.** Dealing with missing values

The PACE Study II methodology and data management have been meticulously designed. Hence, when dealing with missing values, the basic assumption is that data are missing completely at random and non-response is unrelated to any particular group or the actual values of the missing data. Nevertheless, this assumption will still be examined prior to data analysis through the following steps:

**Step 2.1.** Analyse the type of missing values, if known – e.g. refusal or coding error.

**Step 2.2.** Compare the sample of respondents with and without missing values to check for potential variations.

**Step 2.3.** Compare respondents and non-respondents to check for potential variations. This can be

done by using the information given by other respondents regarding the same deceased resident.

To handle missing values, multiple imputation – i.e. a simulation-based approach that takes the uncertainty of the imputed values into account – can be used. With multiple imputation, cases with missing values will still be included in the sample in order to manage potential bias due to non-random deletion of cases.

Each outcome variable will be constructed by summing the value of multiple items and thus missing values may also occur within a certain outcome variable. This study allows missing items not exceeding 30% of the total number of items for each outcome variable. For example, EOLD-CAD is the sum score of 14 symptoms and conditions assessed from a scale of 1 to 3. Only EOLD-CAD data with not more than 4 missing items will be included in the analysis. For EOLD-CAD data with missing items, the sum score will be calculated with a different denominator. This procedure also applies to other outcome variables in the study. The potential impact of missing values on the findings of the study will also be addressed in the Discussion section of papers written with PACE Study II data and the final report of study II.

### **Step 3. Descriptive statistics**

The characteristics of the deceased residents will be described in terms of age, gender, socio-economic status, cause of death or disease underlying death, and functional and cognitive status. The characteristics of the care staff present in participating LTCFs during data collection will be described in terms of age, gender, experience with care, level of education, and palliative care training.

Baseline and post-intervention measurement characteristics will be summarized, both for the control group and the intervention group. The mean and standard deviation or proportion will be given for the descriptive variables. Anova (normal distribution) or Mann-Whitney U-test (non-normal distribution) for continuous, and  $\chi^2$  tests for categorical variables will be used to describe differences between the control group and the intervention group in the baseline and post-intervention measurements and for non-response analysis.

A visual representation of differences in the characteristics of the sample between the control group and the intervention group and between baseline and post-intervention measurements may also be provided by using graphs or plots.

### **Step 4. Conducting statistical analyses to test study hypotheses**

#### ***Intention-to-treat and per protocol analysis***

The primary statistical analyses will use the intention-to-treat (ITT) approach. With the ITT approach, the outcome data from all of the samples who were enrolled and randomized to the intervention group or the control group will be accounted for in the main analyses in the original groups to which they were randomized, regardless of whether or not they completed the PACE Steps to Success training. This approach may reflect the

effects of 'PACE Steps to Success' palliative programme on quality of dying of residents, staff attitudes and knowledge towards palliative care, and quality of palliative care in daily practice.

Per protocol analysis will also be performed. This includes LTCFs which were able to complete the study "according to the protocol". Based on the process evaluation measures, we will determine the cut offs to identify which LTCFs had followed the 'PACE Steps to Success' palliative care programme protocol. Per protocol approach may lower evidence level by introducing attrition bias because those who were only able to attend 2 of the 6 PACE trainings for instance may have different characteristics than those who attended all training sessions. Nonetheless, this approach better reflects the effects of 'PACE Steps to Success' palliative programme on quality of dying of residents, staff attitudes and knowledge towards palliative care, and quality of palliative care when intervention is implemented and taken in an optimal manner.

### ***Regression analyses***

To test the study hypotheses, several regression analyses will be conducted based on the exploration of data and data assumptions, as well as on the data analysis approach to be used (ITT and per protocol). Generally, all primary and secondary outcome measures (scale sum scores) are by nature continuous variables, which would require multivariate linear regression analysis techniques. However, if the assumptions of normal distribution and/or linearity is/are violated, multivariate logistic (or ordinal) regression analyses may be applicable. The specific procedure on how to further analyse skewed or non-linear data will rely upon the decision of the consortium. Basically, multivariate linear or logistic regression analyses may be performed to assess and compare the baseline and post-intervention measurement differences in the outcome measures between the intervention group and the control group, while adjusting for sample characteristics that may differ between groups.

Additionally, multi-level mixed model regression analyses will be performed to account for the baseline measurement and the multilevel nature of the data – e.g. residents and staff nested within LTCFs or country. The kind of multilevel mixed model regression analyses will depend on the nature of the outcome variables and the statistical package to be used for the main analyses.

With the multi-level mixed model analyses, outcomes will be analysed with LTCFs and country as random factor, and group, time point, and their interaction as fixed factors. Differences in mean change (post-intervention measurements minus baseline) between the intervention group and the control group (interaction group\*time) will be calculated. Estimated means with corresponding 95% CI will be reported at baseline and follow-up, both for the intervention and control group. Moreover, estimated differences (and 95%CI) in change between intervention and control are reported. The effect sizes (Cohen's *d*) using the baseline-adjusted mean differences and the variance between residents or care staffs, between LTCFs, and between country will be estimated to assess the magnitude of the effects for the different outcome measures.

All analyses will be two-tailed and considered significant if  $\alpha = 0.05$ . In addition, data will be analysed by using statistical software program suitable for the necessary statistical analyses, such as multilevel mixed model analysis and multiple imputation – e.g. STATA, SAS, or IBM SPSS.

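### The regression model and effect measure for the primary and secondary scores are left to a consortium decision after data exploration, with no fixed test, threshold, cut-point or blinding to allocation.

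*Combined protocol and SAP*

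**What the plan says.** Section I, Step 4, Regression analyses, describes all primary and secondary sum scores as "by nature continuous variables, which would require multivariate linear regression analysis techniques". It then makes an exception: "if the assumptions of normal distribution and/or linearity is/are violated, multivariate logistic (or ordinal) regression analyses may be applicable". On how that would be settled it says: "The specific procedure on how to further analyse skewed or non-linear data will rely upon the decision of the consortium".

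The check itself is in Step 1.3. For continuous variables, "a graphical representation (histogram) or the Shapiro Wilk-test or Kolmogorov Smirnov test can be used to check for normality of the distribution". Nothing says which of the three applies or what result counts as a violation. The section continues: "If the normality of distribution is violated, log-transformation may for example be done". Suspected non-linearity is also referred to the consortium, with quartiles as an example.

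Step 4 adds multilevel mixed models, but lets their kind depend on the outcome variables and on the software. From them it promises the group-by-time difference in mean change, estimated means with 95% confidence intervals, and Cohen's d. Testing is two-sided at 0.05.

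The dementia example under Sub-group data analysis repeats the fallback, naming logistic regression only, and the same consortium decision.

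**The concern.** These clauses govern the five primary scales (EOLD-CAD, QOD-LTC and the three staff scales) and the secondary EOLD-SWC. As written, each could end up with a different model, chosen once its distribution has been seen. Three things are at stake.

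- **Effect measure.** A linear model gives a difference in points. A log transform gives a ratio of geometric means, and a logistic or ordinal model gives an odds ratio. The hypothesis test and the reported effect would depend on the data.
- **Power.** Cutting a score into categories discards information, and the amount depends on a cut-point that the plan does not state.
- **A poorly aimed trigger.** The linear model's normality assumption concerns residuals, which Step 1.3 never mentions. Linearity in a two-level intervention variable cannot fail, because two means always lie on a line. Only covariates can raise that flag, and a logistic model does not cure it, since it assumes linearity on the logit scale.

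**Working it through.** **Inputs from the plan.** Two-sided alpha is 0.05 (end of Regression analyses). EOLD-CAD has 14 items scored 1 to 3 (Step 2), so the sum runs over the 29 integers from 14 to 42. The 80% power in Step 1.1 is only a condition: "T1 and T2 can be used separately for the analysis when statistical power is at least 80" per cent. It is used below as a reference point. The plan gives no sample size, SD, effect size, intracluster correlation or cut-point, so it has no figure of its own to reproduce. Every n, effect size, item correlation and skewness below is an assumption, and respondents are treated as independent.

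**Step 1. Information kept by a binary split of a normal score.** For a cut c with proportion p below it, relative efficiency is e = φ(c)² / [p(1 − p)].

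- Median: 0.3989² / 0.25 = 0.637
- 25/75: 0.3178² / 0.1875 = 0.539
- 20/80: 0.2800² / 0.16 = 0.490
- 10/90: 0.1755² / 0.09 = 0.342

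**Step 2. Information kept by an ordinal model.** Take K equal categories with centred midrank scores s_j, p_j = 1/K and δ_j = φ(c_{j−1}) − φ(c_j). Then e = (Σ s_j δ_j)² / Σ p_j s_j². For K = 4 this is 0.2586² / 0.0781 = 0.856. For K = 3 it is 0.793. On the full score it approaches 3/π = 0.955 (0.952 with 29 equal categories).

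**Step 3. Power.** Starting from 80% with the linear model, power = Φ(2.80 √e − 1.96), and the sample size must grow by 1/e.

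| Model | e | Information lost | Power | N multiplied by |
|---|---|---|---|---|
| Logistic, median split | 0.637 | 36% | 61% | 1.57 |
| Logistic, 25/75 | 0.539 | 46% | 54% | 1.86 |
| Logistic, 20/80 | 0.490 | 51% | 50% | 2.04 |
| Logistic, 10/90 | 0.342 | 66% | 37% | 2.92 |
| Ordinal, 3 categories | 0.793 | 21% | 70% | 1.26 |
| Ordinal, quartiles | 0.856 | 14% | 74% | 1.17 |
| Ordinal, full score | 0.955 | 5% | 78% | 1.05 |

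Cross-check at an assumed standardised difference of 0.3: 175 per arm gives 80.1% power on means. A median split turns this into 44.0% against 56.0%, which has 60.7% power at 175 per arm and needs 275 per arm (275/175 = 1.57).

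**Step 4. Skewed scores.** For a gamma-shaped score with a location shift, a median split has e = 4 f(m)² × variance, where f(m) is the density at the median. The loss is 30% at skewness 1.0, 21% at 1.4 and nil at 2.0.

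**Step 5. How often would a formal test reject?** I used simulated sums of 14 three-level items, with latent inter-item correlation 0.10 to 0.40, item shapes from symmetric to skewed, and 400 runs per setting. Ranges of rejection at the 5% level:

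| n | Shapiro-Wilk | Kolmogorov-Smirnov |
|---|---|---|
| 50 | 8–94% | 0–8% |
| 100 | 12–100% | 0–54% |
| 200 | 29–100% | 2–99% |
| 400 | 93–100% | 26–100% |
| 800 | 100% | 96–100% |

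At n of about 400 or more, Shapiro-Wilk rejects almost always, even when the items are symmetric, because the score is discrete and bounded. At smaller n the answer depends heavily on which permitted check is used.

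**Step 6. Outputs against models.** Estimated means, differences in mean change and Cohen's d come directly from a linear mixed model. A logistic or ordinal model does not give them directly. The plan promises these outputs while leaving the kind of mixed model open, so the two statements do not fit together once the fallback is used.

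**The case against.** The strongest reply is that the text forces nothing. The fallback is permissive, log-transformation is only an example, exploration is placed before the main analysis, and the mixed model with its mean differences is described as something that will be done. On that view the linear mixed model is the real analysis and the rest is contingency.

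Part of this stands, and it rules out several stronger readings that a reader might infer.

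- **That the switch is almost certain.** The plan gives no n, accepts a histogram, and allows Kolmogorov-Smirnov, which often does not reject at n of 200 or less. A failed check does not compel a switch either.
- **That a switch costs about a third of the information.** This is true only of a median split of a near-normal score. The ordinal option costs far less, off-centre splits cost more, and the calculation assumes a shape that the fallback presumes has failed.
- **That the check is made on raw scores.** The plan does not say whether raw scores or residuals are meant. The fair criticism is that residuals are not mentioned.
- **That outcomes will be cut into quartiles.** The passage can equally be read as covering covariates, where categorising is ordinary and leaves the mean difference intact.
- **That an ordinal model is wrong.** It is a legitimate analysis of a bounded score and can serve as a sensitivity analysis.

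What does not stand is the claim that the mixed model settles the matter. It is introduced as an addition and its kind is left to the nature of the outcome, so a score that has been dichotomised would carry that choice into it. Permissive wording does not help either: a choice with no threshold, made with outcome data available and no stated blinding, is not pre-specified.

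**Conclusion.** The concern holds in this form: the plan does not fix the model or the effect measure for its primary and secondary scores, and it allows both to be chosen after data exploration without a rule. That conclusion rests on the text alone. The clause on outputs conflicts with the clause that leaves the model open.

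The size is conditional on a switch being made. From an 80% reference, power falls to about 61% for a median-split logistic model, to between 54% and 37% for splits from 25/75 to 10/90, and to between 78% and 70% for an ordinal model. These figures assume a near-normal score and independent respondents; strong skew can shrink the median-split loss. The documents do not support a statement that the switch will happen, or a single figure for its cost. The point should be addressed before analysis, as the remedy is cheap and gives a better analysis.

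**What to change.** - In Step 4, Regression analyses, name the linear mixed model group-by-time mean difference on the original sum score as the primary analysis for Hypotheses 1 to 3, whatever the normality result. In the sub-group example, do the same for the group-by-time-by-dementia contrast.
- In Step 1.3, check residuals and LTCF effects in place of the raw scores.
- Pre-name cluster-robust or LTCF-level bootstrap confidence intervals for the same mean difference as the sensitivity analysis for non-normality.
- Remove log-transformation, dichotomising and categorising of the outcomes as primary options. Any ordinal model should be named in advance as a sensitivity analysis only.
- Provisions for non-linear covariates may stay, stated as applying to covariates.

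The cost is SAP wording in three places and one sensitivity run. No data collection changes.

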### **Incremental cost-effectiveness ratio**

Incremental cost-effectiveness ratios (ICERs) 'cost per quality increase based on EQ5D-5L utilities' as well as 'cost per quality increase as measured by the QOD-LTC' will be computed. Uncertainty surrounding the ICERs will be determined by using the bootstrap method or the Fieller method.

The ICER (cost per QALY gained) will be transformed in the parameter 'Net Monetary Benefit'. In a regression approach Net Monetary Benefit is the dependent variable. Independent variables are group (PACE, control), LTCF (cluster) and potential confounders. We will estimate 6 models, varying the WTP for a QALY over a range [€0-€100.000] in steps of €20.000 and present the results via a Cost-Effectiveness Acceptability Curve (CEAC). Depending on the skewness of cost (NMB with WTP=0), we will apply a generalized linear model (GLM) approach using a gamma distribution with log link function with cluster robust standard errors. For NMBs with WTP>0 we apply a GLM with log or identity link depending on skewness of the distribution, with cluster robust standard errors.

A cost-effectiveness acceptability curve will be derived that is able to evaluate efficiency by using different thresholds (willingness to pay) for a QALY. The impact of uncertainty surrounding deterministic parameters (for example prices) on the ICER will be explored using one-way sensitivity analyses on the range of extremes. Potential differences in transferability of cost and effect data between countries will be accounted for in scenario analyses.

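### The plan does not say which analysis decides H1-H3: regression without a facility term is offered alongside the multilevel model, and the descriptive tests ignore facility clustering

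*Combined protocol and SAP*

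**What the plan says.** The programme is delivered to facilities. The hypotheses ask whether outcomes are "better in facilities using the 'PACE Steps to Success' palliative care programme than facilities which provide care as usual", per-protocol status in Step 4 is set by LTCF, and the cost-effectiveness plan calls the LTCF the cluster: "Independent variables are group (PACE, control), LTCF (cluster) and potential confounders".

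Step 4 of the outcome plan (Regression analyses) introduces linear regression, with logistic or ordinal regression as the fallback, as the way to test the hypotheses. It then states: "Basically, multivariate linear or logistic regression analyses may be performed to assess and compare the baseline and post-intervention measurement differences in the outcome measures". Adjustment is for sample characteristics. Neither an LTCF term nor a cluster-robust standard error is mentioned.

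The next paragraph begins: "Additionally, multi-level mixed model regression analyses will be performed to account for the baseline measurement and the multilevel nature of the data". That model has random LTCF and country effects and fixed effects for group, time and their interaction. The estimated means, the difference in change with its 95% CI, and Cohen's d are all described in connection with it.

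The section closes with one rule for everything: "All analyses will be two-tailed and considered significant if" alpha = 0.05. The word primary in Step 4 selects intention-to-treat over per-protocol; it does not select a model.

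Step 3 (Descriptive statistics) names "Anova (normal distribution) or Mann-Whitney U-test (non-normal distribution) for continuous, and" chi-square "tests for categorical variables will be used to describe differences between the control group and the intervention group in the baseline and post-intervention measurements", and also for the non-response analysis. The sub-group section repeats both the descriptive tests and the two-part regression text.

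**The concern.** When whole facilities receive the programme, residents and staff in one LTCF are not independent. A test that treats them as independent uses the wrong standard error for a comparison between arms. Step 4 leaves two candidate tests of each hypothesis, one with a facility effect and one without, both judged at 0.05 and unranked. The choice between them could therefore be made after the results are seen, and could fall on a test whose error rate is not 5%.

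The Step 3 tests matter in a smaller way. Their p-values may feed the check of the missing-completely-at-random assumption in Step 2, and may influence which characteristics are treated as differing between groups and so adjusted for.

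The example sub-analysis is offered to partner organisations that will write their own plans, so the ambiguity can spread.

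**Working it through.** The plan gives no sample size, ICC, cluster size or number of LTCFs, so it has no figure of its own to reproduce. From the documents come the two-sided alpha of 0.05 (z = 1.96), the LTCF as cluster, and the group-by-time contrast.

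Assumed, not in the documents:
- ICC 0.05-0.10.
- m = 8-30 respondents per LTCF per wave.
- Correlation of LTCF effects across waves (CAC) 0.6-0.8, with 1 as the fully stable case.
- Different respondents at each wave. This is true of deceased residents. Some staff may appear twice, and that is not modelled.

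**Formulas** (total variance set to 1)
- Arm comparison at one wave: D = 1 + (m - 1) x ICC.
- Single-level group-by-time contrast: D = 1 - ICC + m x ICC x (1 - CAC).
- True type I error of a test that assumes D = 1: 2 x [1 - Phi(1.96 / sqrt(D))].

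**Worked corners**
- One wave, m = 8, ICC 0.05: D = 1 + 7 x 0.05 = 1.35; error 9.2%.
- One wave, m = 30, ICC 0.10: D = 1 + 29 x 0.10 = 3.90; error 32.1%.
- Group-by-time, m = 8, ICC 0.05, CAC 0.8: D = 0.95 + 8 x 0.05 x 0.2 = 1.03; error 5.3%.
- Group-by-time, m = 30, ICC 0.10, CAC 0.6: D = 0.90 + 30 x 0.10 x 0.4 = 2.10; error 17.6%.

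| m | ICC | One wave | Group-by-time, CAC 1 | CAC 0.8 | CAC 0.6 |
|---|---|---|---|---|---|
| 8 | 0.05 | 9.2% | 4.4% | 5.3% | 6.3% |
| 10 | 0.10 | 15.5% | 3.9% | 6.2% | 8.6% |
| 20 | 0.05 | 16.0% | 4.4% | 6.8% | 9.2% |
| 30 | 0.10 | 32.1% | 3.9% | 11.0% | 17.6% |

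Simulation with an assumed 30 LTCFs per arm and 6000 runs agreed. At m = 10, ICC 0.05, one wave gave 9.8-10.8% (formula 10.4%). Group-by-time gave 4.6% at CAC 1 (formula 4.4%), and 6.5% at m = 20, ICC 0.05, CAC 0.8 (formula 6.8%).

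**Does the mixed model as written solve it?** It lists a random LTCF effect but no LTCF-by-time effect. With a random intercept only, the model's residual variance is about (1 - ICC) + ICC x (1 - CAC) x m / (2m - 1), and that variance sets the standard error of the contrast.
- m = 30, ICC 0.10, CAC 0.6: 0.90 + 0.04 x 30/59 = 0.920; ratio 2.10 / 0.920 = 2.28; error about 19%.
- m = 8, ICC 0.05, CAC 0.8: 0.95 + 0.01 x 8/15 = 0.955; ratio 1.03 / 0.955 = 1.08; error about 6%.

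A separate simulation (30 LTCFs per arm, 4000 runs, country omitted) gave 19% against 17% for ordinary regression in the first case, and 6.0% against 5.4% in the second. Below CAC 1, the random-intercept model is no better calibrated than ordinary regression.

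**The case against.** The strongest reply is that the cluster-aware analysis is already the plan's real commitment. The multilevel model *will* be fitted; ordinary regression only *may* be. Every estimate, interval and effect size the plan promises is described with the multilevel model, and no output is specified for the other. A reader might infer that the multilevel model is a mere add-on, or that two p-values per hypothesis are planned. The text supports neither. What remains is that no sentence ranks the two analyses.

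It can also be argued that the linear or logistic text only chooses the model family, with the hierarchy added afterwards. The plan never calls these regressions single-level; that is inferred. But a model introduced as an addition in order to handle nesting implies that the preceding ones do not handle it.

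Step 3 is headed descriptive, and its tests are there to describe. A reader might infer that 9-32% is the error rate for H1-H3. It is not: the hypotheses concern change from baseline, so the figure fits only single-wave arm comparisons. Nor does it carry over to the descriptive tests in the sub-analysis, which compare residents with and without dementia within each arm and so largely within facilities.

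Finally, ignoring clustering does not always inflate the error. With fully stable LTCF effects the single-level group-by-time test runs at 3.9-4.4% over this range. That stands, but the direction of the error cannot be known in advance.

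**Conclusion.** The concern holds in a limited form. The plan leaves the deciding test of H1-H3 undesignated, offers one candidate without a facility term, and commits to descriptive tests that ignore clustering. Under the assumed ICC and cluster sizes, the error is about 9-32% for unadjusted single-wave arm comparisons. For a single-level group-by-time test it is about 5-18% at cross-wave correlations of 0.6-0.8, and slightly below 5% at a correlation of 1. All of these are illustrations; none comes from the documents. Allocation by facility is itself read from the hypotheses and the cost-effectiveness plan.

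This should be fixed, but it does not invalidate the plan, because a multilevel analysis is firmly committed. The Step 3 element is the lesser part. Naming the multilevel model as primary exactly as written would not be enough, since it lacks an LTCF-by-time effect.

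**What to change.** - In Step 4, state that the mixed-model group-by-time contrast is the sole primary test of H1-H3, with random LTCF and LTCF-by-time effects, or with cluster-robust standard errors at LTCF level. The cost-effectiveness plan already uses cluster-robust errors.
- Delete the ordinary linear and logistic regressions from Step 4 and from the sub-group section, or label them sensitivity analyses with cluster-robust standard errors.
- In Step 3 and the matching sub-group text, report means, standard deviations and proportions without p-values, or use LTCF-adjusted tests, including for non-response.

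The cost is a change of wording and, if the regressions go, fewer analyses. The price in precision is a wider interval for the group-by-time contrast than a random-intercept model would report. From the ratios above, the standard error grows by sqrt(1.08) = 1.04 at the mild corner and sqrt(2.28) = 1.51 at the worst, and is essentially unchanged if LTCF effects are stable. Where it widens, the narrower interval would have been too narrow.
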